### Education program

The educational program for participating pharmacists consists of five components: an information session, workshop, toolbox, documentation and an intervision session (Table 2). All sessions are organized in fivefold across Belgium. The feasibility study provided insights in the training needs of pharmacists in Belgium and was used to optimize this educational program.

**Table 2 Tab2:** Overview of the topics in the educational program of the SIMENON study

Education program	Topic			
	Study procedure	Background and evidence based info	Communication skills and patient inclusion	Multidisciplinary collaboration
Information session	X			
Workshop	X		X	X
Toolbox		X		
Documentation	X		X	X
Intervision session	X		X	X

In the first information session interested pharmacists are informed about the aims of the SIMENON study, the procedure of a medicines use review and are given the opportunity to ask questions. In the subsequent obligatory interactive workshop of 2 hours, participants are familiarized with a MUR. The research team of KU Leuven demonstrates a MUR using a simulation patient. Attention is drawn to the drug-related problems that should be detected and its classification (see 7. Outcomes) and to communication skills for patient and GP conversations.

The toolbox supports participants in the analysis phase by providing background information and evidence-based references and websites. The following six topics are addressed, based on the feedback in the feasibility study: geriatric patients and characteristics, drug interactions and side effects, adherence, drug use including time of intake and a written example of a medication review.

The following documentation is available for the community pharmacist: an overview of the steps of a medication review including a checklist, a letter for the GP with study information and a referral letter. For the patients, an information leaflet with informed consent form is foreseen as well as a blank medication list and a brown bag. Finally, an intervision moment is organized halfway in the project for participants to exchange experiences, feedback and tips and tricks for patient inclusions.

### Outcomes

The main outcome of the study is the type and number of drug-related problems and related interventions registered by pharmacists using the validated PharmDISC^2^ classification tool (a process measure) [18]. A second outcome is the impact of the medication review on adherence, objectively measured with medication refill data. A third outcome is the medication related quality of life, measured with the Living with Medicines Questionnaire version 3 (LMQ) [19]. Other patient related outcomes are adherence, self-management, patient satisfaction, use of emergency healthcare services and fall incidents. These outcomes are measured via the pre-post study design using patient questionnaires.

### Data collection

An overview of the data collection strategies is shown in Table 3. Four types of quantitative data are collected: drug-related problems and interventions, medication refill records, patient questionnaires and descriptive pharmacist information. If patients would withdraw consent, no additional data is registered but existing data is preserved.

**Table 3 Tab3:** Overview of the data collected for the SIMENON study

Data collection	A. Drug-related problems & interventions	B. Adherence	C. Questionnaires	D. Descriptive pharmacist information
Subject	Patient	Patient	Patient	Pharmacist
Collector	Pharmacist	Pharmacist	Researcher	Pharmacist
Sample size	900 patients	900 patients	140 patients	75 pharmacies
Method	Questionnaire: webtool	Medication refill records	Questionnaire: by letter, by phone or by e-mail	Questionnaire
Frequency	Four times	Once	Three times	Once
Timeframe	During the medication review process	• 9 months before • 9 months after the review	• 1 week before the review • 3 weeks after the review • 12 weeks after the review	Before start of the study
Content	• Administrative and medical data • DRPs and interventions • Duration • GP contacts	Medication refill records	• Adherence • Self-management • Polypharmacy burden • Satisfaction • Demographic data • Use of emergency healthcare services • Fall incidents	• Pharmacy and Pharmacist characteristics • Pharmacist experiences

For each patient receiving a review, an online registration form is completed by the pharmacist via a webtool (available upon request). Pharmacists are required to login to use this webtool and only coded patient information can be registered. Drug-related problems and interventions are registered throughout the medication review process using the PharmDISC classification system [18]. Permission was given by the authors to translate and use the instrument. Participating pharmacists are given a manual with explanation and examples to ensure the quality of the classification. Medication refill data is collected of all participants in the study to estimate adherence before and after the medication review. Data is collected from 9 months before until 9 months after the review. Finally, all participating pharmacists are required to fill in a questionnaire related to pharmacy and pharmacist characteristics.

The effectiveness of a medication use review is evaluated using patient reported outcomes. Patients are surveyed at three time points by the research team of KU Leuven (Table 4). Based on the preferences of the patient the questionnaires can be completed by e-mail, by phone or by mail. These surveys allow an insight in patient experiences. Table 4 provides an overview of instruments and the time points of data collection. Permission was given by all authors to use the instruments. The ‘Living with Medicines Questionnaire’ and the ‘Patient Satisfaction with Pharmacist Services Questionnaire’ were translated by the researchers in accordance with ISPOR guidelines [20].

**Table 4 Tab4:** Patient related outcome measures. Data is collected 1 week before the patient interview (T_-1w_), 3 weeks later (T_3_) and 12 weeks after the patient interview (T_12w_)

Subject	Instrument	Authors	T_-1w_	T_3w_	T_12w_
Adherence	Probabilistic Medication Adherence Scale (ProMAS)	Kleppe et al. 2015 [21]	X		X
Self-management	Patient Activation Measure (PAM)	Hibbard et al. 2004 [22]	X		X
Polypharmacy burden	Living with Medicines Questionnaire (LMQ)	Krska et al. 2014 [23]	X	X	X
Satisfaction	Patient Satisfaction with Pharmacist Services Questionnaire (PSPSQ) 2.0	Sakharkar et al. 2015 [24]		X	
Demographic data	Living with Medicines Questionnaire (LMQ)	Krska et al. 2014 [23]	X	X	X
Use of emergency healthcare services	/		X		X
Fall incidents	/		X		X

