### Design, setting and study period

The SIMENON study is an intervention study with a pretest-posttest single group design. The intervention is performed by community pharmacists in the primary care setting. Patients are followed over a period of 9 months. Patient recruitment was planned from November 2016 until March 2017.

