### Data analysis

First, descriptive statistics will be used to characterize the study population using demographic parameters, to give an overview of drug-related problems, interventions and level of implementation. Secondly, adherence will be calculated using two methods for the analysis of refill data: the medication possession ratio as well as proportion of days covered. The impact will be measured by comparing data before and after the intervention using appropriate statistical tests for paired data. Subsequently the correlation between objective measures for adherence (medication refill records) and subjective measures (PROMAS score) will be investigated [21]). In addition, the results of these adherence measures will be compared with the registered drug-related problems and interventions. This provides insight in the number of (un)detected adherence problems and the effectiveness of a medication review and interventions to improve adherence.

Third, patient questionnaires will be scored in accordance with the described methods of the original authors. The impact of the intervention will be explored using appropriate statistical tests for paired data. Subgroup analysis will compare the baseline scores in the three types of data collection (letter, phone or email) to ensure the quality of the data.

A final analysis aims to identify patients with a high risk of drug-related problems by investigating the impact of variables on the number of drug-related problems detected by pharmacists. These variables have been defined a priori based on scientific research as well as patient criteria for a medication review in countries abroad. Both patient related factors, process factors and pharmacy related factors will be explored. All analysis will be performed using the statistical program SPSS. A per protocol analysis and a listwise deletion will be applied.

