### Sample size

The study aims to approach 75 pharmacies in Belgium, approximately half in Flanders and half in Wallonia. Each pharmacy in turn includes 12 patients. This brings the total number of participants to 900 (Table 5). The primary aim of this study is to describe the type and number of drug-related problems and related interventions for each patient. In this way, the primary outcome is a process measure. The secondary outcome is medication adherence. A systematic review by Hatah et al. shows that both an intermediate and advanced medication review by community pharmacists significantly improves adherence [7]. Provided that the pharmacist can improve adherence using a medication review in half of the patients with a low adherence (10% of all older patients) and a significance level of 5% and power of 80%, a sample size of 746 patients is calculated [21, 22]. Taking into account a drop-out rate and missing data (17%, *n* = 154) a sample size of 900 participants is proposed.

**Table 5 Tab5:** Sample size

Sample size	Medication review	Questionnaires
Number of Belgian community pharmacies	75	35
Number of participating patients per pharmacy	12	4
Total number of participating patients	900	140

For the patient reported outcomes using questionnaires, all Dutch-speaking patients in the Flemish community pharmacies (approximately 35) are approached. It is hypothesized that 2/3 of patients who consent to a medication review also agree to complete the questionnaires. Considering a drop-out rate of 50%, data should be available for 140 patients (Table 5). In this subset, the score on the Living with Medicines Questionnaire is the main outcome. However, since this instrument has not yet been used in an older polymedicated population, no sample size calculation can be performed.

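### The refill extract has no look-back before the pre-review window, so PDC over the full fixed windows with carry-over would be biased towards improvement

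*Protocol article*

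**What the plan says.** Under Data collection, the protocol article states the purpose of the refill records, "Medication refill data is collected of all participants in the study to estimate adherence before and after the medication review", and their span, "Data is collected from 9 months before until 9 months after the review". Table 3 gives the same span and shows a single collection. No earlier records are mentioned.

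Under Data analysis, "adherence will be calculated using two methods for the analysis of refill data: the medication possession ratio as well as proportion of days covered", followed by "The impact will be measured by comparing data before and after the intervention using appropriate statistical tests for paired data". The design section confirms that there is no comparator: "The SIMENON study is an intervention study with a pretest-posttest single group design".

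The article does not say whether leftover supply is carried into the post-review window, whether the denominator starts at the window edge or at the first fill, or whether the analysis windows equal the whole extract.

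**The concern.** PDC asks, for each day, whether the patient holds medication. To answer that for the first days of a window one must know what was dispensed before it opened. For the post-review window those fills are in the file. For the pre-review window they are not, because the file begins on the same day as the window. A pack collected shortly before month -9 leaves no trace, and the days it covers look like a gap until the next fill.

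The two halves of the paired comparison can therefore be measured differently, with the error on the side of benefit and without any change in behaviour. Refill adherence is the second outcome and the one behind the sample size calculation. The level matters as well as the change: the Data analysis section will set refill adherence against the registered drug-related problems to count detected and undetected adherence problems, and will correlate it with the questionnaire score.

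**Working it through.** The plan states no figure for this effect, so there is none to reproduce. The check is whether a patient whose behaviour never changes would show a change.

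**Inputs**
- Window: 9 months on each side (Data collection, Table 3), taken as 274 days.
- Number of drugs: five or more (patient inclusion criteria).
- Pack length D: not in the document; assumed 28 to 98 days.
- Cut-off for low adherence: not in the document; 80% used for illustration.
- Behaviour: exact on-time refilling, with the window opening at a uniformly distributed point in the refill cycle.

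**Fixed-window PDC with carry-over**

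Let U be the number of days from the start of the pre-review window to the first visible fill, uniform on (0, D).
- Pre-review PDC = 1 − U/274; mean shortfall = (D/2)/274 = D/548.
- Post-review PDC = 100%, because the preceding fills are in the file.
- One drug: P(PDC < 80%) = P(U > 0.2 × 274) = P(U > 54.8) = max(0, 1 − 54.8/D).
- Five drugs: the same probability for the mean of five independent U values.

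| D (days) | Mean shortfall before | Below 80% before, one drug | Below 80% before, mean of five drugs | Below 80% after |
|---|---|---|---|---|
| 28 | 28/548 = 5.1 points | 0% | 0% | 0% |
| 56 | 56/548 = 10.2 points | 1 − 54.8/56 = 2% | about 0% | 0% |
| 90 | 90/548 = 16.4 points | 1 − 54.8/90 = 39% | 21% | 0% |
| 98 | 98/548 = 17.9 points | 1 − 54.8/98 = 44% | 33% | 0% |

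The five-drug column assumes that refill dates are independent across drugs. If all drugs are collected together with the same pack length, the one-drug column applies.

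A separate simulation in whole days agrees: 95.1% before and 100% after at 28 days' supply, 83.8% and 100% at 90 days. It also shows an apparent gain of 4 to 14 points, for supplies of 28 to 100 days, in a patient held at a constant 80%.

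**Other rules on the same extract, no true change (before/after)**

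| Rule | Fully adherent patient | Remark |
|---|---|---|
| MPR by dispensing date | about 100% / 100% | no systematic shift |
| PDC, only fills inside each window | 94.7% / 94.7% at 30 days; 83.8% / 83.9% at 90 days | no spurious change, but the level is too low on both sides |
| PDC from the first fill in each window | 100% / 100% | no spurious change, but real gaps before that fill are lost; a constant 80% patient reads 81% to 85% on both sides |
| PDC, first 100 days used only as run-in, equal windows | 100% / 100% | windows shrink to 274 − 100 = 174 days |

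**With look-back.** Adding 120 days of earlier records gives 100% before and 100% after for every supply length from 28 to 100 days, with both 274-day windows intact.

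**The case against.** The strongest reply is that the article fixes the extract but not the computing rules. The spurious gain needs three things together: analysis windows equal to the full extract, denominators that start at the window edge, and carry-over credited after the review. None is stated, and such rules commonly sit in an analysis plan, which is not shown. One of the two planned measures, MPR, is unaffected when counted by dispensing date. This stands. A reader might infer that adherent patients will appear to improve whatever is done; the document does not support that.

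A reader might also set the 5 to 18 points beside the planned effect. The Sample size section supposes that pharmacists can "improve adherence using a medication review in half of the patients with a low adherence (10% of all older patients"), that is, a fall from 10% to 5% in the proportion of patients with low adherence. A shift in mean PDC is a different quantity, and that section does not define low adherence as PDC below 80%. The two should not be compared directly.

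Likewise, 39% and 44% are one-drug figures with long packs, whereas participants take five or more drugs. With 28-day packs nobody crosses the cut-off.

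Finally, the primary outcome is descriptive, the lack of a control group is acknowledged as a limitation, and recruitment has begun under an approved protocol, so a change is not free.

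What this does not answer is that the date range is a data-collection decision taken in this document. An analysis plan can choose a rule, but it cannot use records that were never drawn. Each rule that works on the existing extract gives something up: the correct level, real gaps, about 100 days of each window, or one of the two planned measures.

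**Conclusion.** The concern holds in conditional form. The extract has no look-back, so PDC over the full fixed windows with carry-over would show a fully adherent patient improving by about 5 points (28-day packs) to 16 to 18 points (90- to 98-day packs). With an 80% cut-off and the mean over five drugs, about 21% (90-day) to 33% (98-day) of fully adherent patients would look low-adherent before the review and none after; with 28-day packs none would. The single-group design cannot remove this.

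These sizes rest on assumed pack lengths, on-time refilling, independent refill dates across drugs and an assumed cut-off. MPR by dispensing date, and PDC with identical first-fill or own-window rules on both sides, carry no spurious change. The point is an inexpensive improvement to the data collection and does not show that the adherence result must be biased.

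**What to change.** Extend the one-off extract by about 3 to 4 months before the pre-review window, to 12 to 13 months before the review. Use the added months only to establish supply on hand when that window opens. Keep the two 9-month windows and apply the same carry-in rule to both.

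If older records cannot be obtained, state that both windows are handled identically: either PDC from the first fill in each window, or the early months as run-in with equal windows on both sides. Report which was used and what it gives up.

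The cost is a longer date range in an extract that each pharmacy already makes once, plus minor programming; there are no extra patients or visits. Participants must regularly obtain their medication from the same pharmacy, so older records plausibly exist there. The downside is more historical data per patient. As ethics approval dates from November 2016 and recruitment started in December 2016, this may need an amendment or consent cover for patients already enrolled.

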### Data management

Patient confidentially is ensured through patient coding during data registration by the treating community pharmacist. Data obtained from the questionnaires are also coded by the researchers. The study database only contains coded data. Data cleaning and analysis is performed by the research group of KU Leuven. All parties of the consortium have access to the final database as stated in the collaboration agreement. Sharing of anonymized individual clinical trial participant-level data is possible for research purposes which are in line with the initial aim of data collection. Data is disseminated through publication in peer reviewed international journals.

### Data analysis

First, descriptive statistics will be used to characterize the study population using demographic parameters, to give an overview of drug-related problems, interventions and level of implementation. Secondly, adherence will be calculated using two methods for the analysis of refill data: the medication possession ratio as well as proportion of days covered. The impact will be measured by comparing data before and after the intervention using appropriate statistical tests for paired data. Subsequently the correlation between objective measures for adherence (medication refill records) and subjective measures (PROMAS score) will be investigated [21]). In addition, the results of these adherence measures will be compared with the registered drug-related problems and interventions. This provides insight in the number of (un)detected adherence problems and the effectiveness of a medication review and interventions to improve adherence.

Third, patient questionnaires will be scored in accordance with the described methods of the original authors. The impact of the intervention will be explored using appropriate statistical tests for paired data. Subgroup analysis will compare the baseline scores in the three types of data collection (letter, phone or email) to ensure the quality of the data.

A final analysis aims to identify patients with a high risk of drug-related problems by investigating the impact of variables on the number of drug-related problems detected by pharmacists. These variables have been defined a priori based on scientific research as well as patient criteria for a medication review in countries abroad. Both patient related factors, process factors and pharmacy related factors will be explored. All analysis will be performed using the statistical program SPSS. A per protocol analysis and a listwise deletion will be applied.

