### Intervention

The intervention consists of a medication use review. In this intermediate medication review both a patient interview and medication refill records are used as information sources to identify drug-related problems with a specific focus on the medicines use of the patient [6]. Table 1 shows the six components of the intervention which is based on the Systematic Tool to Reduce Inappropriate Prescribing (STRIP) tool [17]. A checklist is available for participants to ensure the quality of the medication reviews (available upon request). The feasibility study confirmed the applicability of this six step process and estimated a workload of 120 min per review.

**Table 1 Tab1:** The six-step process of a medication review [17]. The time points of data collection for the SIMENON study are indicated. Both the community pharmacists (CP) and the researchers (R) collect data at different time points

	Component	Time point	Data collection	
Medication review	1 Patient recruitment	T_-1week_	R	
	2 Preparation			CP
	3 Patient interview	T_0_		CP
	4 Pharmacotherapeutic analysis			
	5 Discussing medication list	T_2weeks_		CP
		T_3weeks_	R	
	6 Follow up	T_6weeks_		CP
		T_12weeks_	R	

Upon patient recruitment, the patient is invited for a pharmacotherapeutic anamnesis also referred to as a patient interview [17]. This interview can be either on appointment, during the next visit or immediately upon consent. Patients are encouraged to bring their medication (brown bag method) to this interview and list their current medication. The anamnesis should preferably take place in the pharmacy, if possible in a private area. In exceptional circumstances such as patient immobility, the pharmacist can perform the anamnesis at the patients’ home. In preparation for the anamnesis, the pharmacist consults the medication refill records to review adherence and check drug interactions.

The aim of the patient interview itself is to gain insight in the pharmacotherapy of the patient. Data on medication use, medication knowledge but also experiences are gathered. Additional questions relate to non-medication treatments, lifestyle, living situation, allergies, functional status, hospitalization and fall incidents.

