This study also has several limitations. For one this study is no randomized controlled trial. Although there is no control group, the study provides a detailed description of the drug-related problems and pharmacy interventions. Since many other countries have implemented medication review in the past, this study is on that aspect not very innovative, yet essential since the healthcare system differs across countries and subsequently not all findings are transferable. By using voluntary participation of pharmacists, this creates participating bias. Although the patients should be randomly chosen, it is expected that the most motivated patients who are open to this intervention are included in the study. This also limits the generalizability of the findings. Moreover, the patient follow up is limited to 3 months. Literature suggests this may be rather short to detect an impact on the quality of life [25].

Another limitation of this medication review is that collaborative practice with the general practitioner is not required. Additional input from the GP would indisputably be of added value. However, only a limited amount of initiatives (3/11) in Europe organize case conferences during an intermediate medication review [11]. Moreover, the findings of the feasibility study showed reluctance. Notwithstanding GP collaboration is registered in the webtool and allows subgroup analysis of patients for which multidisciplinary contacts were made.

In conclusion, this study contributes to the evolving role of community pharmacists in Belgium. The findings of this study could provide valuable insights on the drug-related problems that older polymedicated patients experience in Belgium, the patients who would benefit most of a medication review and the value of the community pharmacist in resolving these problems. Therefore, the SIMENON study could significantly support the implementation of medication reviews in Belgium.

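### Comparing refill adherence with registered interventions cannot show that the interventions work, because the refill record that partly prompts them overlaps the 'before' value

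*Protocol article*

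**What the plan says.** Data analysis plans two uses of the refill data. The first is a whole-group comparison of the medication possession ratio (MPR) and the proportion of days covered (PDC): "The impact will be measured by comparing data before and after the intervention using appropriate statistical tests for paired data". The second goes further: "the results of these adherence measures will be compared with the registered drug-related problems and interventions". Of this second step the article says: "This provides insight in the number of (un)detected adherence problems and the effectiveness of a medication review and interventions to improve adherence".

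The Intervention section describes how problems come to be registered. In this type of review "both a patient interview and medication refill records are used as information sources to identify drug-related problems", and before the interview "the pharmacist consults the medication refill records to review adherence and check drug interactions". On the outcome window, Data collection says: "Data is collected from 9 months before until 9 months after the review". The Discussion acknowledges the single-group design: "Although there is no control group, the study provides a detailed description of the drug-related problems and pharmacy interventions".

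The article mentions neither regression to the mean nor a comparison between patients with similar pre-review adherence.

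**The concern.** The refill record has two roles. It helps the pharmacist decide whether a patient has an adherence problem, and it supplies the baseline against which later adherence is judged. A pre-review value can be low because the patient is persistently non-adherent, or because those months were unusually poor or poorly recorded. The second component tends to disappear on re-measurement. Patients flagged partly on a low record will therefore rise on average, and the unflagged will drift down slightly, even if the pharmacist's action does nothing.

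This is the one stated analysis that ties the pharmacist's action to an objectively measured outcome, and refill adherence is the study's second outcome. The study is meant to support the introduction of medication review in Belgium, so a claim that adherence interventions are effective could carry weight that the comparison cannot bear.

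**Working it through.** **Inputs from the article.** Two sources for the flag (refill record and interview); 9 months of refill data on each side of the review; no control group.

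**Inputs assumed, because the article gives none.** Before/after correlation r of 0.6 to 0.8; normally distributed adherence in SD units; about 17% of patients with a registered adherence intervention; no true effect of review or intervention. The article states no figure for this comparison, so there is none to reproduce.

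**Model.** pre = T + E1 and post = T + E2, with Var(T) = r and Var(E1) = Var(E2) = 1 − r. The chance of being flagged is logistic, with logit(p) = −1.9 − score. The score is one of:

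- refill only: pre;
- equal weight: 0.5 × pre + 0.5 × t, where t is T scaled to SD 1 and stands for what the interview reveals about true adherence;
- interview only: t.

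**Closed form for refill only.** Expected change in flagged patients = (1 − r) × (their mean distance below the overall pre-review mean). That distance is 0.73 SD here, so:

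- r = 0.6: 0.4 × 0.73 = 0.29 SD
- r = 0.7: 0.3 × 0.73 = 0.22 SD
- r = 0.8: 0.2 × 0.73 = 0.15 SD

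**Simulation (4 million patients per setting, no true effect).** All values are in SD units.

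| Flag driven by | r | Change in flagged | Post-review level, flagged minus unflagged | Flagged minus unflagged, adjusted for pre |
|---|---|---|---|---|
| Refill only | 0.6 | +0.29 | −0.53 | 0.00 |
| Refill only | 0.7 | +0.22 | −0.61 | 0.00 |
| Refill only | 0.8 | +0.15 | −0.70 | 0.00 |
| Equal weight | 0.6 | +0.15 | −0.61 | −0.15 |
| Equal weight | 0.7 | +0.11 | −0.68 | −0.12 |
| Equal weight | 0.8 | +0.07 | −0.75 | −0.09 |
| Interview only | 0.6 | 0.00 | −0.68 | −0.29 |
| Interview only | 0.7 | 0.00 | −0.73 | −0.24 |
| Interview only | 0.8 | 0.00 | −0.79 | −0.17 |

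The true value in every cell is zero. The whole-group mean change is zero throughout, so the artefact belongs to the comparison by intervention status.

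**A second flag rule.** Here 20% are flagged, by a cut-off on refill plus true adherence plus noise, with an assumed SD of 12 points. The change in flagged minus unflagged patients is +4.0 points at r = 0.6 and +1.9 at r = 0.8. Adjusted for the pre-review value it is −4.5 and −2.7. The pattern is the same.

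**On the point scale**, with the same assumed SD of 12, the spurious gains in the table run from 0.07 × 12 = 0.8 points to 0.29 × 12 = 3.5 points.

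**The case against.** The strongest reply has four parts.

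1. The article does not fix the form of the comparison. It does not say that patients will be split by intervention status, that a paired test will be run among those intervened on, or whether changes or levels will be compared. Such detail may properly sit in a fuller plan. This stands, and it rules out a reading that a reader might infer: that the plan as written will almost always find the interventions to have worked. A comparison of post-review levels would make them look harmful. What remains open to criticism is the stated inference, since neither form supports it.

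2. A reader might infer that interventions are triggered by low refill values alone. The documents do not support this. The interview is named as a second source, and nothing says that pharmacists calculate MPR or PDC, apply a threshold, or look at the same 9 months. This reduces the artefact, by about half under equal weights. It disappears only if the refill record plays no part, which the Intervention section contradicts.

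3. A reader might infer that adjusting for pre-review adherence cures the problem. It does so only if nothing but the refill value and unrelated noise drives the flag. Once the interview carries information on true adherence, the adjusted contrast is biased towards harm by roughly as much as the change in flagged patients is biased towards benefit. Adjustment alone is not an adequate replacement.

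4. The comparison is an addition to a secondary outcome, the article claims only insight, and it concedes the lack of a control group. All true, and this limits the weight of the point. But the general limitation does not warn of this selection effect, and the sentence still names effectiveness as what is learned.

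**Conclusion.** The concern holds in a limited form. The flag for an adherence intervention depends partly on a record that overlaps the baseline of the outcome. A contrast of changes by intervention status is therefore biased towards benefit, and a contrast of post-review levels is biased towards harm. Neither can be read as effectiveness.

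The direction follows from the article's own description, on the ordinary assumption that refill adherence is not perfectly stable over time. The size does not follow from the article: the range of 0.07 to 0.29 SD in flagged patients rests on the assumed correlation, share flagged and relative weight of the two sources.

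The point does not touch the descriptive primary outcome, the whole-group paired test, or the count of detected and undetected adherence problems.

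**What to change.** In Data analysis, for this comparison only:

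- Replace the reference to the effectiveness of interventions to improve adherence with association.
- Report the before/after change in patients with a registered adherence intervention as descriptive only.
- Tabulate change for detected and undetected low adherence within bands of pre-review MPR and PDC.
- Report the contrast by intervention status twice: as unadjusted change, and adjusted for pre-review MPR or PDC. State that the first is biased towards benefit by regression to the mean, and that the second may be biased towards harm because the interview also informs the flag. Treat an effect as suggested only if both agree.

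The cost is a few sentences, one table and one extra regression on data already to be collected. The downside is a more cautious and probably less favourable conclusion about the adherence interventions.
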